## Abstract

**Background:**

Diabetes is a chronic illness, which requires the individual to assume responsibility for their own care with the aim of maintaining glucose and blood pressure levels as close to normal as possible. Traditionally self-management training for diabetes has been delivered in a didactic manner. In recent times alternatives to the traditional delivery of diabetes care have been investigated, for example, the concept of peer support which emphasises patient rather than professional domination. This paper describes the pilot study and protocol for a study that aims to evaluate the effectiveness of a peer support intervention for people with type 2 diabetes in a primary care setting.

**Methods/Design:**

A pilot study was conducted to access the feasibility of a randomized controlled trial of a peer support intervention. We used the MRC Framework for the evaluation of complex interventions. Elements of the intervention were defined and the study protocol was finalized. In this cluster randomised controlled trial twenty general practices are assigned to control and intervention groups. Each practice compiles a diabetes register and randomly selects 21 patients. All practices implement a standardised diabetes care system. In the intervention group all practices recruit three peer supporters. The peer supporters are trained to conduct nine group meetings in their general practice over a period of two years. Each meeting has a structured component. The primary outcomes are blood pressure, total cholesterol, HBA1c and the Diabetes Well-being score. In addition to biophysical, psychosocial, economic and health service utilization data peer supporter activity and qualitative data are collected.

**Discussion:**

Peer support is a complex intervention and evaluating such an intervention presents challenges to researchers. This study will evaluate whether a peer support programme for patients with type 2 diabetes improves biophysical and psychosocial outcomes and whether it is an acceptable, cost effective intervention in the primary care setting.

**Trial registration:**

Current Controlled Trials ISRCTN42541690

## Background

### Improving outcomes in type 2 diabetes

The management of type 2 diabetes has traditionally focused on the lifestyle changes and medication that can improve blood sugar or glycaemic control. However, the United Kingdom Prospective Diabetes Study (UKPDS) and the Steno-2 study highlighted the importance of combining tight glycaemic control and cardiovascular risk reduction such as blood pressure control if long term complications are to be prevented or reduced [1,2]. Two Cochrane reviews of diabetes care concluded that care should be structured with regular prompting for patients and their family doctors; that multifaceted interventions can enhance professional performance and that the addition of patient-oriented interventions can improve outcomes [3,4]. Other research has focused on interventions to change diabetes-related behaviours or interventions that can enhance patient self-management [5,6].

However, more recent international studies failed to make significant impact on biophysical risk factors such as blood pressure, cholesterol and glycosylated haemoglobin (HBA1c) [7-10]. There is evidence that standards of diabetes care are suboptimal in many countries [11,12]. Questions remain as to the type or types of interventions that can significantly improve outcomes in individuals with type 2 diabetes.

### Peer support

Peer support has been formally defined as the "the provision of emotional, appraisal, and informational assistance by a created social network member who possesses experiential knowledge of a specific behaviour or stressor and similar characteristics as the target population, to address a health-related issue of a potentially or actually stressed focal person" [13]. This definition of peer support falls within the social support model, which is defined as the process through which social relationships might promote health and well-being [14]. A peer may have a greater understanding of an individuals situation than a member of their own family or social network who may feel uncomfortable about an issue or may be too upset to provide support [15]. Within the social support model, the direct effect model would postulate that peer support could reduce feelings of isolation and loneliness, provide information about access to health services or the benefits of behaviours that positively improve health and well-being and encourage more positive health practices [13].

Qualitative studies with people with type 2 diabetes have highlighted the value they place in learning from the experience of others [16] and the potential gap between knowledge and understanding, with a need for more "understandable information" in "layman's language" [17]. This could be addressed through a peer support intervention. A peer supporter is a type of lay health worker, who are defined in a Cochrane review as individuals who carry out functions related to health care delivery; are trained in some way in the context of an intervention and have no formal related professional or paraprofessional qualification [18]. The use of non-professional volunteers has improved outcomes in other diverse health settings such as maternal child health development [19] and cardiac surgery [20]. A participatory intervention using lay facilitators with womens' groups led to a significant reduction in neonatal mortality [21]. The dramatic success of this intervention has been attributed in part to the 'remarkable capacity and altruism' of the lay women facilitators but also to the fact that it was a well-targeted demand-side intervention [22].

Unlike the peer led educational interventions such as the Chronic Disease Self-Management Programme (CDSMP) [23] devised by Kate Lorig the intervention in this study focuses more on social support than education.

### Evaluation of peer support

Peer support is a complex intervention and ideally should be evaluated using a framework such as the Medical Research Council Framework for Development and Evaluation of Randomised Controlled Trials for Complex Interventions to Improve Health [24]. This framework highlights the importance of adequate modelling and exploration or piloting of the intervention prior to commencement of the full randomised controlled trial. It stresses the importance of comparing a fully defined intervention with an appropriate alternative and ensuring that the intervention can be replicated to facilitate long-term implementation. The importance of a process evaluation of a randomised controlled trial, which incorporates a qualitative component and includes a consideration of treatment fidelity, has also been emphasized [25-28]. We have used the MRC framework to develop the peer support intervention for this study and this process is described in detail elsewhere (submitted to BMC Health Services Research, in press). There is also increasing recognition of the importance of a parallel health economic analysis when carrying out a randomised controlled trial of an intervention with potential to improve health outcomes [29]. Costs must be considered when evaluating new treatments and this is particularly the case for a condition such as type 2 diabetes, which has enormous costs for individuals and healthcare systems [30].

## Methods/Design

### Pilot study

The pilot study was carried out in two general practices, one a small single-handed practice and the other a large group practice. Both practices have a practice nurse and computerized record systems. Twenty four patients and four peer supporters from the practices participated. Some characteristics of the participants are presented in Table 1. The peer supporters, who were selected by the GPs, attended two evening training sessions conducted by the research team. Each peer supporter facilitated three sessions with participating patients. These sessions were held in the general practices for approximately an hour and a half.

**Table 1 T1:** Personal characteristic of the patients and peer supporters that participated in the pilot study

	**Patient participants**	**Peer supporters**
Male	13 (59%)	4 (100%)
Mean age (yrs)	66	65
Mean (yrs) since diagnosis of type 2 diabetes	4	7
Entitled to medical card	14 (64%)	2 (50%)
Smoker	3 (14%)	0 (0%)

The qualitative evaluation of the pilot study indicated that patients were positive about their experience of peer support-"very helpful because you are going into a hospital, seeing a doctor, but you are not seeing other people who have it like ourselves" (FG1, Participant 3). The patients were also positive regarding the professional diabetes education services but many felt that healthcare professionals may not be familiar with the day to day issues which arise when living with diabetes. Patients felt that a peer would serve as a motivating factor in both encouraging diabetes behaviours and in lifestyle modification. Peer supporters described the experience as "very positive" (FG7 Participants 4,5). They reported that the patients in their groups were interested in simple practical information- "the people are not looking for a theoretical understanding of it, you know they don't want to know the latin" (FG7, Participant 6). Potential barriers, such as confidentiality and intrusiveness were dismissed by patients and peer supporters. Payment was largely viewed as against the spirit of peer support though participants felt expenses should be covered. Practice staff reported that the patients appeared to enjoy the contact with each other and the study had little negative impact on their work or the day to day running of the practice.

These pilot results are in keeping with a recent UK study looking at the role of lay health advisers in diabetes [31]. Health professionals and patients were interviewed and both were broadly supportive of the concept of lay advisors following the development of lay criteria, structured training and guidelines. Patients indicated a preference for a lay advisor over an unknown health professional and they identified the ability of lay advisors to enhance and support diabetes patient self-management. Several peer support or 'buddy' projects are being piloted in the UK though none are currently being evaluated using a rigorous methodology such as a randomised controlled trial [32].

### Randomised controlled trial

#### Objective

To determine whether a peer support programme for patients with type 2 diabetes improves biophysical and psychosocial outcomes and whether it is an acceptable, cost effective intervention in the primary care setting

The study is a cluster randomised controlled trial where general practices are allocated into one of two groups:

1. Control practices: implement a standardised diabetes care system for the 21 study patients (see below).

2. Intervention practices: implement the standardised diabetes care system and the peer support intervention (see below)

#### Identification and recruitment of practices and patients

##### Practice identification

Twenty practices will be identified from the Trinity College/Health Service Executive General Practice Training Programme and the Trinity College network of undergraduate teaching practices. They all have a practice nurse and vary from single-handed practices to multi-partner practices with the largest practice having five full time equivalent partners. They include a mixture of urban, suburban and rural practices.

The GP's are provided with information about the study. They are then contacted by the research team and asked if they are interested in participating in the study. If they agree to participate the project manager visits the practice and discusses the study in more detail. During this meeting the project manager gets commitment to the study and one GP and practice nurse are identified as managing the programme at practice level. Participating practices are given a grant of €5000 per annum for three years (€1000 of which is allocated to the practice nurse). Practices are eligible to participate if they have a practice nurse; have computerized records; did not participate in the pilot study; have a minimum GMS (General Medical Services scheme, see Table 2) list of approx 1000 patients and/or have > 50 patients on their register of patients with type 2 diabetes; and are not participating in an existing shared care diabetes programme involving structured care between the general practices and hospital diabetes service.

**Table 2 T2:** The General Medical Services scheme

THE GENERAL MEDICAL SERVICES SCHEME [33]
-Free medical and surgical health services for those on low income and for everyone over 70 yrs of age
-An eligible person is entitled to select a General Practitioner of their choice, from those doctors who have entered into agreements with the Health Service Executive
-29.5% of the population are entitled to a medical card

##### Patient identification (21 patients per practice)

Participating practices compile a list of eligible patients from their practice to create or update their diabetes register. A combination of approaches to compile the register are used including personal recollection of practitioners, identification of patients through computerized prescribing of diabetes related medications and if necessary using computerized records of local pharmacies. Diagnosis of type 2 diabetes is confirmed by double-checking patient records. Only patients agreeing to participate in the intervention and who provide baseline data collection will be recruited into the trial. Details of those declining to participate will be recorded including age, gender, GMS status, duration of diabetes and diabetes treatment. A patient is eligible to participate if they are over 18 years of age; have type 2 diabetes and attend participating practices. A patient will be excluded if they have significant mental or physical illness which is likely to impair their capacity to participate in the programme

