#### Randomisation

##### Practice allocation

Practices will be stratified by practice size (less than two or two or more whole-time-equivalent GPs) and presence of existing structure primary diabetes care service. They will then be allocated to intervention or control groups using minimization [34]. Allocation will be carried out independently of the research team. It will occur prior to patient identification and baseline data collection. While it is regarded as best practice to randomize after baseline data collection, in this study allocation must take place in this sequence to facilitate the recruitment of peer supporters from the patient register in intervention general practices before the randomisation of patients and the beginning of the intervention.

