##### Patients: random selection

Once a complete diabetes register is established, the project manager assists the practices in using a list of random numbers to select patients for participation. All patients on the register are allocated a number 1 to Y (where Y is the total number of patients on the list). Randomly selected patients are sent an invitation letter, information sheet and reply slip. Patients who do not respond in two weeks are contacted by telephone by the practice nurse to ascertain interest in participation. If a patient does not meet the eligibility criteria or declines to participate the next patient is selected from the list until the quota of 21 is reached. (Figure 1)

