#### Informed consent and ethical approval

An invitation and information sheet is sent to the randomly selected eligible patients. Patients are asked to sign and return a reply slip if they are interested in participating. They are contacted by the practice nurse and an appointment is made for them to visit the practice for baseline data collection. Prior to baseline data collection the practice nurse reads the information sheet to the patient, allowing them to ask any questions and confirming their willingness to participate in the study. The practice nurse then asks the patient to sign the consent form.

Ethical approval has been obtained from the Ethics Committee of the Irish College of General Practitioners (Protocol No.: REC0904-11; 01/12/04)

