### Data analysis

All results will be analysed using STATA statistical software [44] which has a facility for complex survey sample analysis that allows for adjustments in data analysis based on design effects, planned or unplanned. Analyses will be carried out using two approaches:

• by intention to treat i.e. including all randomized patients, regardless of their participation in the intervention.

• Sensitivity analyses will explore whether adherence to the intervention influences the effect of the intervention on primary outcomes

Participating patients will be described in terms of:

• Age

• Gender

• Date of diabetes diagnosis

• Single/Multimorbidity

• Socioeconomic status

Practices will be described as follows:

• Number of GPs (WTE)

• Number of practice nurses (WTE)

• Number of administrative staff (WTE)

• Practice size (No of GMS patients and total number of patients)

• Practice geographical location

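### The entry rule asks patients to agree to the intervention after practices have been allocated; read as written, it could enrol different kinds of patient in the two arms

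*Protocol article*

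**What the plan says.** Under Patient identification: "Only patients agreeing to participate in the intervention and who provide baseline data collection will be recruited into the trial". Agreement to the intervention and provision of baseline data are two separate conditions.

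Under Practice allocation, on when allocation takes place: "It will occur prior to patient identification and baseline data collection". The stated reason is that "in this study allocation must take place in this sequence to facilitate the recruitment of peer supporters from the patient register in intervention general practices". Staff in intervention practices therefore know their arm before any patient is invited.

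The Objective section defines the arms. Both deliver standardised diabetes care; intervention practices add peer support. The Intervention section describes that addition as nine group meetings over two years.

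Under Patients: random selection, the rule for filling each practice's places, of which there are 21, begins: "If a patient does not meet the eligibility criteria or declines to participate the next patient is selected from the list until the quota of". The practice nurse telephones non-responders. Under Informed consent, the nurse reads out the information sheet and confirms willingness to take part in the study; "The practice nurse then asks the patient to sign the consent form".

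The Data analysis section defines the main analysis as "by intention to treat i.e. including all randomized patients, regardless of their participation in the intervention".

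**The concern.** In a cluster trial that recruits patients after allocation, the arms are comparable only if the same kind of patient enters in each. A condition that refers to the intervention threatens this, because one arm has meetings to accept or refuse and the other has none.

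Willingness to attend a group for two years could be related to motivation, adherence or well-being, and so to all four primary outcomes. If it filters entry in one arm only, part of any difference at two years would reflect who was enrolled rather than what peer support did. A larger sample would estimate the same biased quantity more precisely.

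**Working it through.** The plan gives no figure on this point, so there is none to reproduce. The first step is a reading of the text; the second and third are illustrations of size.

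**Step 1. One patient, two practices.** Take a patient who accepts follow-up but not group meetings, and apply the rules literally.

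| | Intervention practice | Control practice |
|---|---|---|
| What is offered | Standardised care plus nine peer meetings | Standardised care |
| Agrees to the intervention? | No | No peer support to refuse |
| Recruited? | No; next patient on the list is taken | Yes; counts towards the 21 |
| In the intention-to-treat set? | No | Yes |

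The article describes no question to control patients about willingness to attend groups, and no recruiter unaware of the arm.

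**Step 2. Size of the entry gap.** Let q be the share of otherwise recruitable patients who would accept meetings, and d the mean of acceptors minus the mean of refusers. With no treatment effect, the intervention mean is the acceptors' mean and the control mean is q × acceptors' mean + (1 − q) × refusers' mean. Their difference is

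gap = (1 − q) × d.

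Inputs from the article: well-being SD 10.3 and target difference 5; HbA1c SD 1.6 and target difference 0.9%. Assumptions, which the article does not supply: q from 0.5 to 0.8, d from 0.3 to 0.5 SD.

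- Well-being, low: 0.2 × 0.3 × 10.3 = 0.6 points (12% of 5). High: 0.5 × 0.5 × 10.3 = 2.6 points (52% of 5).
- HbA1c, low: 0.2 × 0.3 × 1.6 = 0.10% (11% of 0.9). High: 0.5 × 0.5 × 1.6 = 0.40% (44% of 0.9).

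**Step 3. Effect on the false-positive rate, HbA1c.** Assume 10 practices of 21 per arm and 80% follow-up: 210 × 0.8 = 168 analysed per arm, 16.8 per practice. With the article's ICC of 0.001, the design effect is 1 + (16.8 − 1) × 0.001 = 1.016, and SE = 1.6 × √(2 × 1.016 / 168) = 0.176. The two-sided rejection rate with no true effect is Φ(gap/SE − 1.96) + Φ(−gap/SE − 1.96). Here d is in HbA1c percentage points; 0.3 and 0.5 are 0.19 and 0.31 SD.

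| d | q | gap | Rejection rate (nominal 5%) |
|---|---|---|---|
| 0.3 | 0.8 | 0.06 | 6.3% |
| 0.3 | 0.6 | 0.12 | 10.5% |
| 0.3 | 0.4 | 0.18 | 17.6% |
| 0.5 | 0.8 | 0.10 | 8.8% |
| 0.5 | 0.6 | 0.20 | 20.6% |
| 0.5 | 0.4 | 0.30 | 40.0% |

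Steps 2 and 3 assume that the whole entry gap persists to two years and that the analysis is unadjusted. If d = 0 or q = 1, the gap is zero.

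**The case against.** The strongest reply is that the asymmetry is not stated. The article gives one rule and one recruitment procedure for all practices, and its consent section speaks of willingness to join the study. The word intervention may be loose: a nurse training session given to all practices is dated by the start of the intervention. The information sheet, which would settle what each arm was asked, is not shown. This stands, and it limits the point to what the sentence says when read literally. It does not remove the point, because a sentence that meant only consent to the study would still need correcting.

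The article also has safeguards. Patients are drawn at random from a complete register with the project manager's help. Decliners' characteristics and reasons are recorded, and the outcomes are measured at baseline. These allow any imbalance to be described and partly adjusted for, though not for unmeasured motivation. The allocation order is openly acknowledged and justified, but that justification concerns recruiting peer supporters and does not require patients to agree to meetings.

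A reader might infer four stronger points that the article does not support.

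- **That the illness exclusion also differs by arm.** It refers to capacity to take part in the programme, but the article uses that word for activity in all practices and for standardised care as well as for peer support.
- **That the rule contradicts the intention-to-treat definition.** Agreeing is not attending. Recruited patients who never attend remain in the analysis, and the planned adherence analysis presupposes them.
- **That acceptability is measured on a truncated denominator.** Acceptability is addressed by the qualitative evaluation, not by an uptake rate.
- **That the bias must favour peer support.** Isolated or poorly controlled patients might be the keener ones, which would reverse it.

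**Conclusion.** The concern holds as a risk created by the wording. Agreement to the intervention, allocation before recruitment, peer support in one arm only and replacement of decliners together allow willingness to attend groups to filter entry in one arm. Intention to treat starts after that filter and cannot undo it.

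The conclusion rests on reading the intervention as peer support, as the article's own Intervention section does, and on control patients not being asked an equivalent question, about which the article is silent. Size and direction are unknown. The illustrated gaps run from about a tenth to about half of the target differences, but they depend wholly on assumed values and show only that the problem could matter.

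**What to change.** Replace the sentence under Patient identification with one entry rule for every practice: the patient consents to the study and its data collection. Use the same invitation and information sheet in all 20 practices, stating that some practices will offer peer meetings and that attendance is not a condition of entry. Keep patients who consent to data collection but decline the meetings, and analyse them in the arm to which their practice was allocated.

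Compare the number, characteristics and reasons of decliners by arm, using the records already planned, and adjust each primary outcome for its baseline value, which is already collected.

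The change is to wording only and leaves the allocation order alone. It should precede the first invitations, because patients never enrolled cannot be recovered in analysis; after that, only the decliner comparison and baseline adjustment remain. The price is lower attendance and some dilution of the effect in the intervention arm. Recruiting nurses would still know their arm, so the decliner comparison remains necessary.
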